#### Process Variables

Additionally, secondary outcomes will include process variables as potential mechanisms of change to understand the underlying intervention effects. These will include the following measures:

*Cognitive and behavioral responses to symptoms* will be measured using the Cognitive and Behavioural Responses Questionnaire—Short Form (CBRQ-SF). This study will use an adapted version of the CBRQ-SF [57], including 5 subscales from the CBRQ-SF: symptom focusing (3 items), damage beliefs (3 items), embarrassment avoidance (3 items), all-or-nothing behavior (3 items), and fear avoidance (3 items) subscales. Additionally, we will include the catastrophizing subscale (4 items) from the original CBRQ [58]. Items are rated on a 5-point Likert scale ranging from “strongly disagree” to “strongly agree.” Each of the subscales in the shortened and original CBRQ have been shown to be reliable and valid [57,58].*Acceptance of illness* will be measured using the Acceptance of Chronic Health Conditions Scale, which has demonstrated reliability and validity in chronic conditions [59]. This 10-item scale scores items on a 5-point Likert-scale from 1 (“strongly agree” to 5 (“strongly disagree”). Items were adapted to include “MS” in the wording. Items pertaining to positive attitudes toward the condition are reverse scored. Higher scores therefore indicate higher levels of acceptance of the condition.*Intolerance of uncertainty* will be measured using the Intolerance of Uncertainty Scale-12 item [60]. The 12-item scale is rated on a 5-point Likert scale ranging from 1 (“not at all characteristic of me”) to 5 (“entirely characteristic of me”). Items on the questionnaires are summed, and therefore scale scores can range from 12 to 60.*Expression of emotion* will be measured using the Beliefs about Emotions Scale [61]. This 12-item scale assesses beliefs about the unacceptability of expressing and experiencing negative emotions. Each item is responded to on a 7-point Likert scale ranging from 0 (“totally disagree”) to 6 (“totally agree”). The scale is scored by summing the items, and thus the total scores can range from 0 to 72. High scores on the scale represent a greater belief that it is unacceptable to express emotions.*Health-related behaviors*, such as smoking status and alcohol use (average weekly consumption), will also be recorded.

### Sample Size

The target patient sample size for the study, consisting of 75 participants for the COMPASS-MS intervention, was determined based on pragmatic considerations of the number of people living with MS attending the MS service and the prevalence of distress. The objective of the mental health screening is to assess all eligible people living with MS attending the MS clinic during the study period. However, we conservatively estimate a 50% consent rate for screening, resulting in 500 out of 1000 patients completing the screening. Based on findings from Boeschoten et al [4], we anticipate that 30% of these screened patients (n=150) will experience distress. If 50% of these distressed patients find the treatment acceptable, we will achieve our target sample size of 75.

As this is a real-world implementation study, a formal power calculation was not performed; however, a sample of 75 provides sufficient precision to estimate implementation metrics and detect a moderate within-group effect size (Cohen *d*=0.32‐0.35) on the primary outcome with 80% power at an α level of .05. We acknowledge that the study may be underpowered for moderator analyses or subgroup comparisons, particularly if attrition is moderate.

### Statistical Methods and Data Analysis

Most Reach and Implementation outcomes will be summarized descriptively. Categorical variables will be summarized with frequencies and percentages, while continuous variables will be reported as means and SDs or as medians with IQRs, depending on the distribution. Where relevant, rates (eg, eligibility, adherence) or mean differences (eg, change from baseline) will be presented alongside 95% CIs to quantify uncertainty in estimates. In the screened sample, differences in psychological distress, depression, and anxiety between key demographic characteristics (age, gender, and ethnicity) and any interaction effects will be examined using linear regressions. For between-group comparisons (eg, demographic and clinical differences between referred patients vs those who consent to COMPASS-MS and COMPASS-MS participants with baseline data only vs COMPASS-MS participants with complete data), chi-square test, Mann-Whitney *U* test, and two-tailed independent sample *t* tests will be conducted, depending on the distribution of the variable.

Potential effectiveness will be assessed using mixed effects linear regression, including a random intercept to account for repeated measurements within participants. Assessment time points will be modeled as dummy-coded covariates to estimate change from baseline, adjusting for demographic and relevant clinical variables. Interaction terms between time and covariates will be tested to explore whether the change from baseline differs across subgroups. Effect sizes will be reported as standardized mean differences, using the adjusted mean change from baseline from the mixed-effects models and the pooled SD (treating baseline as the control). Mixed-effects models will handle missing data using full-information maximum likelihood, under the missing-at-random assumption. Missing item-level data within self-report measures will be handled using proration when at least 50% of items are completed.

A per-protocol sensitivity analysis will be undertaken for potential effectiveness outcomes, restricted to participants who fully adhered to the treatment protocol (≥5 online sessions and attending ≥3 appointments). Moreover, moderator analyses are exploratory and will be conducted for the primary effectiveness outcome with the intention-to-treat sample to examine the heterogeneity of the treatment effect across MS subtype, age, gender, ethnicity, and education level.

To address the risk of type I error due to multiple testing of secondary outcomes and mechanisms, we will correct for multiple statistical comparisons by using a Holm-Bonferroni correction method. The interpretation of findings will prioritize the primary effectiveness (PHQ-ADS) and core RE-AIM implementation outcomes to ensure a focused evaluation of the intervention. Long-term follow-up beyond 12 weeks is not part of this study design; however, service-level reach data will be tracked over an 18-month implementation period.

Qualitative data will be analyzed using an inductive thematic analysis for the interviews with stakeholders, incorporating an iterative constant comparison approach. Conversely, patient interviews will be analyzed using a framework technique to enable comparisons with other COMPASS studies (eg, Jones et al [62]). Coding will be completed line-by-line by members of the research team, with regular discussions to refine coding frameworks and record analytic reflections. Interviews with patients and health care professionals will be analyzed and reported separately. Data collection and analysis will occur concurrently to allow emerging insights to inform subsequent interviews. NVivo software (Lumivero) will be used to facilitate data management and analysis.

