### Study Procedures

#### Procedure: Patient Participants

The route of routine screening (MyChart vs clinician referral) and whether a patient completes a psychological assessment will be pseudoanonymized, recorded, and shared with the research team. For patients who complete a psychological assessment, demographic information (age, gender, ethnicity, and index of multiple deprivation) and clinical information (depression, anxiety, cognitive impairment, and disability) will be collected to determine the appropriate treatment pathway (more details are given in the “Implementation Measures” and “Effectiveness Measures” sections).

Following patient screening and assessment, eligible and interested patients who have consented to share their contact details will be contacted by the research team. Patients will be emailed the information sheet and a link to the informed consent form. Upon receipt of consent, a link to the baseline questionnaire (pretreatment) will be sent. Following its completion, patients will be enrolled in COMPASS-MS. Patients will complete a follow-up questionnaire 12 weeks after baseline (posttreatment). All recruitment procedures will be conducted remotely via telephone or the Qualtrics online platform [44]. Pre- and posttreatment questionnaires will also be administered through Qualtrics. These questionnaires will assess the potential effectiveness of COMPASS-MS. Additionally, eligible patients will have the option to consent to participate in a qualitative interview study. A subgroup, purposively sampled to capture sociodemographic diversity and different levels of engagement with COMPASS-MS, will be invited to take part in an interview about their experience with the integrated pathway.

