#### Reach

Reach will describe the population who participate in the intervention. This will include the number, percentage, and characteristics of people living with MS who:

Complete routine screening and psychological assessment.Report clinical levels of psychological distress at assessment. Associations between distress and demographic or clinical characteristics will also be assessed.Meet the inclusion criteria for COMPASS-MS and consent to the COMPASS-MS study? Reach will also be assessed by comparing the demographic characteristics of patients who were referred to the study and those who consented to participate in COMPASS-MS.

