### Implementation Measures

#### Reach

Data collected during screening and triage to determine appropriate treatment pathways will include the number, percentage, and characteristics of patients who (1) agree to and complete routine screening for psychological distress via MyChart; (2) receive a direct referral from a clinician for psychological distress after the identification of distress during a consultation; (3) complete psychological assessment; (4) are interested in receiving psychological support; (5) report clinical levels of psychological distress, depression, or anxiety at the time of assessment, and their sociodemographic predictors of these outcomes also evaluated; (6) report their distress as related to their experience with MS; (7) report the presence of active suicidal risk; (8) express interest in participating in the COMPASS-MS study; (9) meet the inclusion criteria for COMPASS-MS and provide consent to participate in the COMPASS-MS study, evaluating differences in demographic characteristics compared with those referred; and (10) receive COMPASS-MS but are subsequently identified during treatment as requiring more intensive treatment.

The characteristics that will be evaluated are as follows: (1) demographic information (age, gender, ethnicity, and index of multiple deprivation); (2) depression and anxiety measured using the PHQ-8 [42] and GAD-7 [43], respectively; (3) mild cognitive impairment assessed using the Montreal Cognitive Assessment telephone version [45,46]; and (4) Expanded Disability Status Scale score [47], which is clinician-reported based on an examination by a neurologist, with ranges from 0 to 10 in 0.5-unit increments, with higher scores reflecting greater disability.

For those who consent and complete the pretreatment questionnaire, data will be gathered on sociodemographic factors (age, gender, ethnicity, and index of multiple deprivation) and clinical factors (MS type, year of diagnosis, comorbidities, commonly occurring MS symptoms, relapse history in the last 12 wk, and medication to treat relapses).

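### The Reach comparison of referred patients with consenters uses independent-groups tests although, as written, the consenters are also in the referred group, so the tests are strongly conservative and can miss unequal uptake

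*Protocol article*

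**What the plan says.** Three places in the protocol article describe the comparison.

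- Outcomes, Reach: part of Reach is assessed by "comparing the demographic characteristics of patients who were referred to the study and those who consented to participate in COMPASS-MS". No test is named.
- Implementation Measures, Reach, item 9: consenters are counted, "evaluating differences in demographic characteristics compared with those referred". No test is named.
- Statistical Methods and Data Analysis: the between-group comparisons include "demographic and clinical differences between referred patients vs those who consent to COMPASS-MS". For these, chi-square, Mann-Whitney U and "two-tailed independent sample *t* tests will be conducted, depending on the distribution of the variable".

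None of the three limits the referred group to patients who did not consent. The order of events is given under Procedure: Patient Participants: "Following patient screening and assessment, eligible and interested patients who have consented to share their contact details will be contacted by the research team". The information sheet and consent form come after that contact.

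The other example in the same analysis sentence, "COMPASS-MS participants with baseline data only vs COMPASS-MS participants with complete data", does form two separate groups.

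**The concern.** All three named tests assume that no patient is in both groups. If every consenter was first referred, the comparison sets a part against the whole that contains it. This has two effects, both towards a null result. The observed difference is diluted because the consenters appear on both sides. The standard error is overstated because the test ignores the positive covariance between the two group means.

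The comparison asks whether those who take up treatment differ from those offered the route to it. Implementation is one of the coprimary objectives, and the analysis section ranks the main RE-AIM outcomes with PHQ-ADS when findings are interpreted. A test that almost never rejects is a poor basis for a statement about who the pathway reaches.

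**Working it through.** **Inputs.** The protocol states no figure for this comparison and does not give the number referred. The nearest figures are in the Sample Size section: "we anticipate that 30% of these screened patients (n=150) will experience distress" and "If 50% of these distressed patients find the treatment acceptable, we will achieve our target sample size of 75". They reproduce: 1000 × 0.50 = 500 screened; 500 × 0.30 = 150 distressed; 150 × 0.50 = 75 consenting. The 150 is the expected number distressed and is used here only as a proxy for the number referred. The Results section reports 82 patients recruited. I assume two-sided testing at 5% and equal variances.

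**Formulas.** Let m consenters lie inside a referred group of T, with common SD s and a true difference d (in SD units) between consenters and non-consenters.

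- Expected observed difference: d(1 − m/T).
- True variance of that difference: s²(1/m + 1/T − 2/T) = s²(1/m − 1/T), because the covariance of the two means is s²/T.
- Variance assumed by an independent-groups test: s²(1/m + 1/T).

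**With T = 150 and m = 75.**

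- Shrinkage factor: 1 − 75/150 = 0.5.
- True SE: √(1/75 − 1/150) = 0.082 SD.
- Assumed SE: √(1/75 + 1/150) = 0.141 SD.
- Under the null the test statistic has SD 0.082/0.141 = 0.577 instead of 1.
- Type I error: P(|Z| > 1.96/0.577) = 0.069%. Simulation with 40,000 runs gave 0.06% for the t test and 0.08% for chi-square. The disjoint comparison gave 4.9% and 4.8%.
- Power at d = 0.5, overlapping groups: the statistic has mean 0.5 × 0.5/0.141 = 1.77 and SD 0.577, so power is P(Z > (1.96 − 1.77)/0.577), about 37%. Simulation gave 33%.
- Power at d = 0.5, disjoint 75 vs 75: 0.5/√(2/75) = 3.06, and P(Z > 1.96 − 3.06) is about 86%.

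**Other assumed sizes.** The last column is the power of the overlapping test at the difference for which the disjoint test has 80%.

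| Referred T | Consenting m | Type I error | Power (disjoint = 80%) |
|---|---|---|---|
| 300 | 82 | 0.947% | 58% |
| 150 | 50 | 0.557% | 51% |
| 200 | 75 | 0.365% | 46% |
| 150 | 75 | 0.069% | 28% |
| 150 | 82 | 0.029% | 21% |
| 150 | 100 | 0.001% | 6% |

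The effect worsens as the consenting share rises, and it never reverses.

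**Illustration (invented counts).** Suppose 15 of 75 consenters and 30 of 75 non-consenters have some characteristic. Uptake is then 15/45 = 33% among those with it and 60/105 = 57% among those without.

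- Disjoint test, 15/75 vs 30/75: a 20-point difference, chi-square 7.14, p = 0.008.
- Comparison as worded, 15/75 vs 45/150: a 10-point difference, chi-square 2.56, p = 0.11.

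**The case against.** The strongest reply is that the wording is shorthand. The comparison is given as an example, under between-group comparisons, with tests for independent samples, and its companion example is disjoint. The authors may well mean referred patients who did not consent, and a fuller plan may say so. That is possible, but the test names are the only textual support for it. All three places name the referred group without restriction, and an analyst who followed them would build overlapping groups.

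Several further objections stand and limit the point.

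- Only the analysis section attaches tests. Setting consenters beside everyone referred is a legitimate description of representativeness, so the two Reach passages are not wrong in themselves.
- The term referred is not defined. The article separates patients found through MyChart from those referred directly by clinicians, and elsewhere speaks of referral to the study. If only clinician referrals are meant, the overlap is partial and the formulas above do not apply exactly. Clinician-referred consenters would still be counted twice.
- The 150 is a proxy, so the 0.07% is one scenario and not a figure implied by the plan.
- A reader might infer that unequal uptake will be concealed and reach declared equitable. The protocol does not support that. It calls for numbers, percentages and characteristics at each stage, where a difference would remain visible. It also attaches no decision rule to these p-values and nowhere plans to read non-significance as equity.

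**Conclusion.** The point holds for the tested comparison in the analysis section. As written, the groups overlap and the named tests do not apply. The error is conservative: it misses differences and does not create them. On the proxy of 150 referred and 75 consenting, the contrast is halved, type I error is about 0.07%, and power at 0.5 SD is 33-37% instead of about 86%. Across the other splits tried, type I error runs from about 0.001% to 0.9%. These figures assume that the consenters are fully nested in the referred group and that variances are equal.

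Severity is moderate. A reader might be tempted to treat this as a defect that undermines the study's main result. It does not: the PHQ-ADS analysis does not use this comparison, and this is one supporting element among ten listed Reach measures.

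**What to change.** In Statistical Methods and Data Analysis, define the referred group and test consenters against patients who were referred and assessed but did not consent. The named tests can stay. An equivalent option is to model consent (yes/no) among all referred and assessed patients, for example by logistic regression. Report the difference, or the model estimate, with a 95% CI. Align the contrast in the two Reach passages, and keep the full referred group as a descriptive column only.

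With 75 vs 75, this restores the type I error to about 5% and gives 80% power at d = (1.96 + 0.84) × √(2/75) = 0.46.

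The cost is a change of wording and one grouping variable. Procedure: Patient Participants provides for demographic and clinical characteristics only for patients who complete the psychological assessment. The comparison therefore describes uptake among assessed patients and says nothing about losses between referral and assessment, which should be stated. The article reports that analysis has not started, so the change can be made before results are seen.

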## Methods

### Study Design

This real-world longitudinal, single-arm study includes 2 nested qualitative studies. Quantitative data will be collected at pretreatment and posttreatment (12 wk). This protocol is aligned with the SPIRIT (Standard Protocol Items: Recommendations for Interventional Trials) guidelines (Checklist 1), which has been adapted for single-arm, nonrandomized studies.

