### Limitations

This study employs a single-arm, observational design within 1 specialist MS clinic conducted within a specific UK NHS context. The lack of a control group means that observed changes in distress cannot be definitively attributed to the intervention, as natural symptom fluctuation or regression to the mean may occur. Moreover, findings may have limited generalizability to different MS service models across the United Kingdom or to international health care systems with varying structures and resources. Furthermore, the 12-week follow-up period precludes assessment of the long-term sustainability of clinical benefits or implementation success. Future multicenter RCTs will be required to confirm these preliminary findings.

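### The exploratory moderator analysis is worded as treatment-effect heterogeneity, which a single arm cannot estimate, and it names education level, which the article does not list as collected

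*Protocol article*

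**What the plan says.** Study Design states that "This real-world longitudinal, single-arm study includes 2 nested qualitative studies".

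Statistical Methods and Data Analysis describes the subgroup work twice. In the paragraph on the mixed model: "Interaction terms between time and covariates will be tested to explore whether the change from baseline differs across subgroups". In the next paragraph, "moderator analyses are exploratory and will be conducted for the primary effectiveness outcome with the intention-to-treat sample", with the aim to "examine the heterogeneity of the treatment effect across MS subtype, age, gender, ethnicity, and education level".

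On data, Procedure: Patient Participants says that at psychological assessment "demographic information (age, gender, ethnicity, and index of multiple deprivation) and clinical information (depression, anxiety, cognitive impairment, and disability) will be collected". The Reach part of Implementation Measures says that, for those completing the pretreatment questionnaire, "data will be gathered on sociodemographic factors (age, gender, ethnicity, and index of multiple deprivation", together with "clinical factors (MS type, year of diagnosis, comorbidities, commonly occurring MS symptoms, relapse history in the last 12 wk, and medication to treat relapses".

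Limitations says that, without a control group, "observed changes in distress cannot be definitively attributed to the intervention", and gives natural symptom fluctuation and regression to the mean as the reasons.

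**The concern.** Two things do not fit together.

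First, the moderator sentence promises a quantity that the design does not provide. Saying that a treatment effect varies across subgroups requires an estimate of that effect within each subgroup, and so some measure of what would have happened there without treatment. With one arm there is none. Followed as written, the plan would report a subgroup difference in pre-post change as effect modification.

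Second, the moderator list and the data lists disagree on education level. A reader cannot tell from the article whether that part of the analysis can be done.

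Both are worth settling now, because the Results section says data analysis has not started.

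**Working it through.** **The plan's own figure, as background.** Sample Size gives a detectable within-group effect of d = 0.32 to 0.35 with 75 participants, 80% power and α = .05. Assuming a two-sided test, the normal approximation gives (1.960 + 0.842)/√75 = 0.324, and the paired t test (noncentral t) gives 0.328. The upper end, 0.35, corresponds to about 67 completers. The range reproduces, and nothing below changes it.

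For a two-group comparison of change, the detectable difference in SDs of change is 2.802 × √(1/n₁ + 1/n₀):
- 50:50 split of 75: 0.65
- 75:25 split: 0.75
- 85:15 split: 0.91

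The plan already acknowledges low power for moderators, so this is context and not part of the point.

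**Step 1. Moderators against listed data.**

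| Moderator | Listed as collected? |
|---|---|
| MS subtype | Yes, as MS type in the pretreatment questionnaire (Reach) |
| Age | Yes, in all three demographic lists |
| Gender | Yes, in all three |
| Ethnicity | Yes, in all three |
| Education level | In none of them |

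The three lists are the assessment list (Procedure: Patient Participants), the Reach characteristics and the pretreatment questionnaire (both in Reach). Each gives the same four items, with deprivation index as the fourth, and none is marked as a set of examples. Education is also absent from the usage and fidelity data (Implementation) and from the outcome, service-use and process measures (Effectiveness Measures), which go down to smoking and alcohol. As a variable it appears only in the moderator sentence. Four of the five moderators are covered.

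**Step 2. What the interaction estimates.** For subgroup g, write mean pre-post change as τ_g + ν_g, where τ_g is the treatment effect and ν_g is the change that would have occurred without treatment. The time-by-covariate interaction between subgroups 1 and 0 is then

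(τ₁ + ν₁) − (τ₀ + ν₀) = (τ₁ − τ₀) + (ν₁ − ν₀).

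Heterogeneity of treatment effect is the first bracket. A single arm identifies only the sum. The two are equal only if ν₁ = ν₀, and the study has no untreated group in which to check that.

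**Step 3. How large the second bracket could be.** None of these inputs is in the documents; they are assumptions: PHQ-ADS with population mean 12 and SD 10, entry at a score of 10 or more, no treatment effect, and subgroups that differ only in retest correlation ρ.

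- Mean excess over the population mean among those selected: 10 × φ(−0.2)/[1 − Φ(−0.2)] = 10 × 0.391/0.579 = 6.75.
- Expected change: −(1 − ρ) × 6.75.
- ρ = 0.8 gives −1.35; ρ = 0.7 gives −2.03; ρ = 0.6 gives −2.70.

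The apparent interaction is therefore 0 when both subgroups have ρ = 0.8, about 0.7 points for 0.8 against 0.7, and 1.35 points for 0.8 against 0.6. A simulation of the first and last cases gave the same 0 and 1.35. Against the 4-point minimum important difference in Effectiveness Measures, 1.35/4 is about a third.

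This shows that the artefact is possible, not how large it is here. The real entry rule is PHQ-8 or GAD-7 of at least 5 at an assessment that precedes the baseline questionnaire, so some regression to the mean may already have happened by baseline.

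**The case against.** The best defence is that most of the needed caution is already in the article. The mixed-model paragraph states the quantity correctly as a difference in change from baseline. The moderator analyses are labelled exploratory and confined to the primary effectiveness outcome. Sample Size concedes low power. Interpretation is to prioritise the PHQ-ADS and the core implementation outcomes. Limitations names regression to the mean and calls for randomised trials. On this view one loose phrase sits beside a correct description and a general caveat.

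Much of that stands, and it is why the severity is modest. It does not remove the point. Exploratory status and low power warn of imprecision, whereas the problem is what is being estimated: a larger sample would not turn differential change into effect modification. The Limitations caveat concerns overall change and is not carried over to the moderator sentence.

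On education, a reader might infer that it was never recorded and that the analysis cannot be run. The documents do not support that. The questionnaire is not shown, and an article may list fewer items than were asked. Nor does completed recruitment show that it went unrecorded. What can be said is that the article's own lists disagree.

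A reader might also infer that deprivation should have been a moderator because it is collected, or that moderator results will be used to direct tailoring or roll-out to particular subgroups. No passage commits to either.

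**Conclusion.** The point holds in two limited parts.

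1. The stated aim of the moderator analysis exceeds what a single-arm design can estimate. This follows from the design and needs no numerical assumption. Only the illustrative size, 0 to 1.35 points under the assumed values, depends on assumptions.
2. One of five named moderators, education level, is missing from every list of collected variables in the article. This is a mismatch to reconcile, not evidence that the data do not exist.

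It would be too strong to say that the plan flatly contradicts its Limitations section. The caveat is there in general form and has simply not been applied to this analysis. The primary pre-post analysis, the sample size and the power statement are unaffected.

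**What to change.** **Wording.** In Statistical Methods and Data Analysis, describe the analysis as exploratory predictors of change from baseline, in line with the section's own mixed-model paragraph. Add that no conclusion on differential treatment effect will be drawn from it.

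**Education.** If it was recorded, add it to the pretreatment list under Reach. If not, drop it as a moderator. Deprivation index could be added as an exploratory predictor, but it measures something different from education and is not a required substitute.

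**Baseline severity, if wanted.** Use a separate sensitivity model of the 12-week PHQ-ADS on baseline PHQ-ADS and the covariate. Do not add baseline PHQ-ADS as a covariate to the repeated-measures model, where it is already one of the responses. The separate model needs its own statement on missing 12-week scores, and it would not remove subgroup differences in natural course.

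**Cost.** Two wording changes and, if the sensitivity model is used, a little extra analysis. The study gives up any claim to have identified moderators of the treatment effect.
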